aOrdinal logistic regression model, adjusting for baseline participants' views, age and chronic lung disease status

**Supplementary Table 5.** POCTRM result for participants allocated to the intervention group, with subsequent prescription of antibiotics and antivirals.

|                                 | Number of cases
(N=)                              | Number prescribed
antibiotic at
appointment 2             | Number prescribed
antiviral at
appointment 2              |
|---------------------------------|------------------------------------------------------|-----------------------------------------------------------------|-----------------------------------------------------------------|
|                                 | n (% of participants
in POCT RM group) | n (% of participants
with this POCT RM
result) | N (% of participants
with this POCT RM
result) |
| No valid result                 | XX (XX%)                                             | XX (XX%)                                                        | XX (XX%)                                                        |
| No microbe detected             | XX (XX%)                                             | XX (XX%)                                                        | XX (XX%)                                                        |
| Single microbe detected  |                                                      |                                                                 |                                                                 |
| Bordetella pertussis            | XX (XX%)                                             | XX (XX%)                                                        | XX (XX%)                                                        |
| Bordetella parapertussis        | XX (XX%)                                             | XX (XX%)                                                        | XX (XX%)                                                        |
| Chlamydia pneumoniae            | XX (XX%)                                             | XX (XX%)                                                        | XX (XX%)                                                        |
| Mycoplasma pneumonia            | XX (XX%)                                             | XX (XX%)                                                        | XX (XX%)                                                        |
| Influenza A no subtype detected | XX (XX%)                                             | XX (XX%)                                                        | XX (XX%)                                                        |
| Influenza A H1                  | XX (XX%)                                             | XX (XX%)                                                        | XX (XX%)                                                        |
| Influenza A H1-2009             | XX (XX%)                                             | XX (XX%)                                                        | XX (XX%)                                                        |
| Influenza A H3                  | XX (XX%)                                             | XX (XX%)                                                        | XX (XX%)                                                        |
| Influenza B                     | XX (XX%)                                             | XX (XX%)                                                        | XX (XX%)                                                        |
| Adenovirus                      | XX (XX%)                                             | XX (XX%)                                                        | XX (XX%)                                                        |
| Coronaviruses HKU1              | XX (XX%)                                             | XX (XX%)                                                        | XX (XX%)                                                        |
| Coronaviruses NL63              | XX (XX%)                                             | XX (XX%)                                                        | XX (XX%)                                                        |
| Coronaviruses 229E              | XX (XX%)                                             | XX (XX%)                                                        | XX (XX%)                                                        |
| Coronaviruses OC43              | XX (XX%)                                             | XX (XX%)                                                        | XX (XX%)                                                        |
| Coronaviruses Mers-CoV          | XX (XX%)                                             | XX (XX%)                                                        | XX (XX%)                                                        |
| Coronaviruses SARS-CoV-2        | XX (XX%)                                             | XX (XX%)                                                        | XX (XX%)                                                        |
| Human Metapneumovirus           | XX (XX%)                                             | XX (XX%)                                                        | XX (XX%)                                                        |
| Human Rhinovirus/Enterovirus    | XX (XX%)                                             | XX (XX%)                                                        | XX (XX%)                                                        |
| Parainfluenza 1                 | XX (XX%)                                             | XX (XX%)                                                        | XX (XX%)                                                        |
| Parainfluenza 2                 | XX (XX%)                                             | XX (XX%)                                                        | XX (XX%)                                                        |
| Parainfluenza 3                 | XX (XX%)                                             | XX (XX%)                                                        | XX (XX%)                                                        |
| Parainfluenza 4                 | XX (XX%)                                             | XX (XX%)                                                        | XX (XX%)                                                        |
| RSV                             | XX (XX%)                                             | XX (XX%)                                                        | XX (XX%)                                                        |

Supplementary Table 5 continued.

|                            | Number of cases
(N=)                              | Number prescribed
antibiotic at
appointment 2             | Number prescribed
antiviral at
appointment 2              |
|----------------------------|------------------------------------------------------|-----------------------------------------------------------------|-----------------------------------------------------------------|
|                            | n (% of participants
in POCT RM group) | n (% of participants
with this POCT RM
result) | N (% of participants
with this POCT RM
result) |
| Multiple microbes detected |                                                      |                                                                 |                                                                 |
| Combination 1              | XX (XX%)                                             | XX (XX%)                                                        | XX (XX%)                                                        |
| Combination 2              | XX (XX%)                                             | XX (XX%)                                                        | XX (XX%)                                                        |
| ...                        | XX (XX%)                                             | XX (XX%)                                                        | XX (XX%)                                                        |

**Supplementary Table 6.** Change in clinician response to “I believe that an antibiotic is needed is needed to treat the patient’s illness” prior to and post-randomisation in the two allocated groups: per protocol set, percentages are of the total number of clinicians, within the allocation / test result group, responding to the question at both time points

|                                                           |                            | Clinician views after randomisation and, in the intervention group, learning the POCTRM result |              |                                   |                 |                          |
|-----------------------------------------------------------|----------------------------|------------------------------------------------------------------------------------------------------------------|--------------|-----------------------------------|-----------------|--------------------------|
|                                                           |                            | Strongly agree                                                                                            | Agree | Neither agree nor disagree | Disagree | Strongly disagree |
| POCTRM group, positive result for virus |                            |                                                                                                                  |              |                                   |                 |                          |
| Clinician view pre-randomisation                   | Strongly agree             | XX (XX%)                                                                                                         | XX (XX%)     | XX (XX%)                          | XX (XX%)        | XX (XX%)                 |
|                                                           | Agree                      | XX (XX%)                                                                                                         | XX (XX%)     | XX (XX%)                          | XX (XX%)        | XX (XX%)                 |
|                                                           | Neither agree nor disagree | XX (XX%)                                                                                                         | XX (XX%)     | XX (XX%)                          | XX (XX%)        | XX (XX%)                 |
|                                                           | Disagree                   | XX (XX%)                                                                                                         | XX (XX%)     | XX (XX%)                          | XX (XX%)        | XX (XX%)                 |
|                                                           | Strongly disagree          | XX (XX%)                                                                                                         | XX (XX%)     | XX (XX%)                          | XX (XX%)        | XX (XX%)                 |
| POCTRM group, negative result for virus |                            |                                                                                                                  |              |                                   |                 |                          |
| Clinician view pre-randomisation                   | Strongly agree             | XX (XX%)                                                                                                         | XX (XX%)     | XX (XX%)                          | XX (XX%)        | XX (XX%)                 |
|                                                           | Agree                      | XX (XX%)                                                                                                         | XX (XX%)     | XX (XX%)                          | XX (XX%)        | XX (XX%)                 |
|                                                           | Neither agree nor disagree | XX (XX%)                                                                                                         | XX (XX%)     | XX (XX%)                          | XX (XX%)        | XX (XX%)                 |
|                                                           | Disagree                   | XX (XX%)                                                                                                         | XX (XX%)     | XX (XX%)                          | XX (XX%)        | XX (XX%)                 |
|                                                           | Strongly disagree          | XX (XX%)                                                                                                         | XX (XX%)     | XX (XX%)                          | XX (XX%)        | XX (XX%)                 |
| No POCTRM group                         |                            |                                                                                                                  |              |                                   |                 |                          |
| Clinician view pre-randomisation                   | Strongly agree             | XX (XX%)                                                                                                         | XX (XX%)     | XX (XX%)                          | XX (XX%)        | XX (XX%)                 |
|                                                           | Agree                      | XX (XX%)                                                                                                         | XX (XX%)     | XX (XX%)                          | XX (XX%)        | XX (XX%)                 |
|                                                           | Neither agree nor disagree | XX (XX%)                                                                                                         | XX (XX%)     | XX (XX%)                          | XX (XX%)        | XX (XX%)                 |
|                                                           | Disagree                   | XX (XX%)                                                                                                         | XX (XX%)     | XX (XX%)                          | XX (XX%)        | XX (XX%)                 |
|                                                           | Strongly disagree          | XX (XX%)                                                                                                         | XX (XX%)     | XX (XX%)                          | XX (XX%)        | XX (XX%)                 |

**Supplementary Table 7.** Number of adverse events per participant

|                                                                        | Intervention (n=XX) | Control (n=XX) |
|------------------------------------------------------------------------|---------------------|----------------|
| Number of related* adverse events                        |                     |                |
| 0 events                                                               | XX (XX%)            | XX (XX%)       |
| 1 event                                                                | XX (XX%)            | XX (XX%)       |
| 2 events                                                               | XX (XX%)            | XX (XX%)       |
| 3+ events                                                              | XX (XX%)            | XX (XX%)       |
| Number of Serious Adverse events                         |                     |                |
| 0 events                                                               | XX (XX%)            | XX (XX%)       |
| 1 event                                                                | XX (XX%)            | XX (XX%)       |
| 2 events                                                               | XX (XX%)            | XX (XX%)       |
| 3+ events                                                              | XX (XX%)            | XX (XX%)       |
| Number of related* serious adverse events                |                     |                |
| 0 events                                                               | XX (XX%)            | XX (XX%)       |
| 1 event                                                                | XX (XX%)            | XX (XX%)       |
| 2 events                                                               | XX (XX%)            | XX (XX%)       |
| 3+ events                                                              | XX (XX%)            | XX (XX%)       |
| Number of suspected unexpected serious adverse reactions |                     |                |
| 0 events                                                               | XX (XX%)            | XX (XX%)       |
| 1 event                                                                | XX (XX%)            | XX (XX%)       |
| 2 events                                                               | XX (XX%)            | XX (XX%)       |
| 3+ events                                                              | XX (XX%)            | XX (XX%)       |

\*Possibly, probably or definitely related to the intervention or trial procedures

**Supplementary Table 8.** List of participants formally withdrawing from all further participation in the study

| Reason for withdrawal | Days after
randomisation |
|------------------------------|-------------------------------------|
| Intervention group    | XX                                  |
|                              | XX                                  |
|                              | XX                                  |
|                              | XX                                  |
| Comparison group      | XX                                  |
|                              | XX                                  |
|                              | XX                                  |
|                              | XX                                  |
|                              | XX                                  |

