## 6.6 Randomisation (Day 1)

### Figure 1, Step 4

Participants will be individually randomised 1:1 to intervention (GP POCTRM test) or control (No GP POCTRM test) using an internet-based randomisation system developed and maintained by Sealed EnvelopeTM. Randomisation will be stratified by age (<16 years vs. ≥16 years) and chronic lung disease (present vs. absent). It will not be possible to blind the allocated randomisation group since the subsequent processes for each group differ.

The Study Champion or Clinician randomises participants and immediately informs (if necessary) the Study Clinician which group the participant has been allocated to.

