## 10. STATISTICS AND HEALTH ECONOMICS ANALYSIS

### 10.1 Sample Size Calculation

#### 10.1.1 Clinical Sample Size

Antibiotic prescribing at the index consultation is the primary outcome measure. The largest individual patient data meta-analysis to date reported the use of antibiotics in 51,780 patients in observational and 55,682 patients in experimental studies, across a wide spectrum of respiratory infections and patient groups, similar to those we propose to recruit in RAPID-TEST. In both observational and experimental studies, immediate and delayed antibiotics were prescribed to 47% and 18% respectively (total 65%).

We anticipate factors both increasing and decreasing antibiotic prescribing in the control group of the RAPID-TEST trial. Patients in whom clinicians have the most uncertainty regarding antibiotics will be selected (suggesting an average 50% prescribing rate) but it is known that antibiotics are often prescribed 'just in case'.

Previous stewardship trials of POCTs have used varying minimum clinically important difference (MCID) definitions of absolute prescribing reductions, from 10% to 20%, with actual reductions observed of 15% and 22%. Since POCTRMs are expensive, we selected a MCID of 15%.

Assuming an antibiotic prescribing rate of 60% in the control group, 244 participants per group will allow a true reduction to 45% in the GP POCTRM test group to be detected with 90% power at 5% significance. A total randomisation target of 514 will allow for 5% attrition. This number will provide at least 90% power to detect the same absolute difference if the antibiotic prescribing rate is found to be higher or lower than 60% in the control group.

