## 2.7. SAMPLE SIZE CALCULATION

Assuming an antibiotic prescribing rate of 60% in the control group, 244 participants per group will allow a true reduction to 45% in the POCT group to be detected with 90% power at 5% significance. A total randomisation target of 514 will allow for 5% attrition. This number will provide at least 90% power to detect the same absolute difference if the antibiotic prescribing rate is found to be higher or lower than 60% in the control group.

If the POCT results in fewer antibiotic prescriptions, we wish to demonstrate non-inferiority of the POCT in terms of not increasing mean symptom severity at days 2 to 4 to a clinically significant extent. Assuming 80% completion of Trial Diaries (as previously achieved in adults and children) we will have data for symptom severity at 2 to 4 days in 206 participants per group. Data on 7,000 adults and children managed without POCT indicates a mean symptom severity at days 2 to 4 of 2.3 (standard deviation 1.5). We know this measure's distribution is positively skewed and have used a calculation that accommodates this (assuming equal skew in both groups, quantified as a coefficient of variation of 0.7). Assuming, in truth, no difference between groups, 206 participants in each group will give 90% power for a one-sided 95% confidence interval to exclude increases in the average symptom score of 20% or more.

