### 4.4. SUBGROUP ANALYSES FOR PRIMARY OUTCOME

Three pre-specified subgroup analyses will be conducted for the primary outcome (**Table 2**, see section 5):

Age <16 years versus 16+ years. We hypothesize that, due to less information about symptoms being provided by children, the information from the POCTRM will reduce antibiotic prescriptions to a greater extent in children.

Presence or absence of chronic lung disease. We hypothesize that general practitioners will tend to “play it safe” and prescribe an antibiotic to those with chronic lung disease, and there will be less of an impact of the POCTRM on antibiotic prescribing in that group.

Disagreement (or not) between the general practitioner and the patient in whether an antibiotic is needed. We hypothesize there will be a greater impact of the POCTRM in reducing antibiotic prescribing when the patient believes an antibiotic is needed (agree or strongly agree with this statement) but the general practitioner strongly disagrees or disagrees that an antibiotic is needed,

or is uncertain. In this situation, evidence from the POCTRM that the RTI may have a viral cause may reduce the likelihood of the general practitioner being persuaded to prescribe an antibiotic.

If there is evidence of superiority for the POCTRM group compared to the control group on the key secondary outcome of symptom severity over days 2 to 4, the above subgroup analyses will also be conducted for that measure (and presented in a separate supplementary table).

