|                                                                                |                                |                         |                                                        |                    |
| Participant – Doctor disagreement at baseline c                     |                                |                         |                                                        | 0.XXX b |
| Yes                                                                            | XX/XXX (XX%)                   | XX/XXX (XX%)            | XX.XX (XX.XX, XX.XX)                                   |                    |
| No                                                                             | XX/XXX (XX%)                   | XX/XXX (XX%)            | XX.XX (XX.XX, XX.XX)                                   |                    |
|                                                                                |                                |                         |                                                        |                    |
| Causal mechanistic analysis – per protocol population                   |                                |                         |                                                        |                    |
| Virus detected on POCT RM (comparison group result from laboratory) |                                |                         |                                                        | 0.XXX b |
| Yes                                                                            | XX (XX%)                       | XX (XX%)                | XX.XX (XX.XX, XX.XX)                                   |                    |
| No                                                                             | XX (XX%)                       | XX (XX%)                | XX.XX (XX.XX, XX.XX)                                   |                    |

a. Odds ratio and confidence interval, from a logistic regression model, adjusting for participant age and chronic lung disease status

b. p-value for interaction term, testing the null hypothesis of equal odds ratios in the population between the two subgroups

c. Participant believes antibiotics are needed to treat the RTI, doctor does not believe or is unsure that antibiotics are needed

**Table 3** Symptom measures

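### SAP 4.4 predicts how far POCT will reduce prescribing in each subgroup but names no scale and tests only odds ratios; if prescribing in chronic lung disease is very high, a smaller absolute reduction can look like an equal or stronger effect

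*Combined protocol and SAP*

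**What the plan says.** SAP 4.4 lists three pre-specified subgroup analyses of the primary outcome, each with a direction. The reduction is expected to be larger in children than in adults. It is expected to be larger where the patient thinks an antibiotic is needed and the clinician does not, or is unsure. For chronic lung disease, the SAP expects clinicians to be cautious and to "prescribe an antibiotic to those with chronic lung disease, and there will be less of an impact of the" test there. No scale is named for any of the three.

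The shell of Table 2 (SAP Section 5) shows, for each subgroup, the count and percentage prescribed by arm and an odds ratio with its 95% confidence interval. Each pair of subgroups gets one p-value, defined in footnote b as the "p-value for interaction term, testing the null hypothesis of equal odds ratios in the population between the two subgroups". No risk difference, risk ratio or interaction on another scale is planned.

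Protocol 10.1.1 discusses the size of effect that matters in terms of "definitions of absolute prescribing reductions" and concludes "we selected a MCID of 15"%. SAP 2.7 builds the sample size on that figure: "Assuming an antibiotic prescribing rate of 60% in the control group, 244 participants per group will allow a true reduction to 45"%. The stated power for this difference is 90%, with a 5% significance level. On losses, the same section says: "A total randomisation target of 514 will allow for 5% attrition".

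**The concern.** An odds ratio and a risk difference rank two subgroups the same way when control risks are similar, but not necessarily when they differ. The reasoning given for chronic lung disease is that clinicians lean towards prescribing there anyway, which points to higher control prescribing in that subgroup. Close to 100%, a small absolute fall corresponds to a large relative change in the odds. The pattern the SAP predicts, fewer prescriptions avoided in chronic lung disease, could then sit on the null of the only planned test, or could appear with the opposite sign.

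What is at stake is the reading of a secondary result. A report could say that the test works about equally well in chronic lung disease, on the strength of similar odds ratios and a large interaction p-value, when the number of prescriptions avoided per 100 patients differs substantially.

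**Working it through.** **Inputs from the documents.** Control rate 60%, POCT rate 45%, 244 analysed per group, 90% power, 5% significance, 5% attrition, 514 randomised (SAP 2.7); 1:1 allocation (protocol 6.6); absolute minimum important difference of 15 points (protocol 10.1.1).

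**Inputs that the documents do not give.** Control prescribing in chronic lung disease (varied below from 70% to 95%) and its prevalence among participants (varied from 10% to 40%). These are assumptions.

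**Step 1: reproduce the plan's figure.** Pooled-variance formula for two proportions, mean rate 0.525:

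n = [1.960 × √(2 × 0.525 × 0.475) + 1.282 × √(0.60 × 0.40 + 0.45 × 0.55)]² / 0.15² = 230.8, rounded up to 231.

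With continuity correction: (230.8/4) × [1 + √(1 + 4/(230.8 × 0.15))]² = 244 per group. Then 488/0.95 = 513.7, rounded up to 514. Both stated figures reproduce.

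**Step 2: put the design effect on the odds-ratio scale.** (0.45/0.55)/(0.60/0.40) = 0.545.

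**Step 3: hold that odds ratio fixed and vary the control rate.** For control rate p, the POCT odds are 0.545 × p/(1 − p), and the POCT rate is odds/(1 + odds). Example at 90%: 0.545 × 9 = 4.909, and 4.909/5.909 = 83.1%.

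| Control rate | POCT rate at OR 0.545 | Absolute reduction |
|---|---|---|
| 60% | 45.0% | 15.0 points |
| 70% | 56.0% | 14.0 points |
| 75% | 62.1% | 12.9 points |
| 80% | 68.6% | 11.4 points |
| 85% | 75.6% | 9.4 points |
| 90% | 83.1% | 6.9 points |
| 95% | 91.2% | 3.8 points |

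Every row satisfies the null of footnote b against the 60% row. Up to about 75% the reductions are close to 15 points. From about 85% they are clearly smaller.

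**Step 4: can the sign reverse?** A 10-point fall from 90% to 80% is an odds ratio of 4/9 = 0.444, and from 85% to 75% it is 3/5.667 = 0.529. Both are stronger than 0.545 for 15 points from 60%. Likewise 50% to 35% is 0.538, weaker than 0.444. So reversal is possible at high control rates.

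**Step 5: power of the interaction on each scale.** This is a Wald approximation with 488 analysed. For the log odds ratio, the variance is the sum over the four cells of 1/[n p(1 − p)]. For the risk difference, it is the sum of p(1 − p)/n. Power is two-sided at 5%. Participants without chronic lung disease are taken as 60% to 45%.

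- Chronic lung disease 90% to 83.1%: odds-ratio test 5% (its null is true); risk-difference test 12% to 19% over 10% to 40% prevalence.
- Chronic lung disease 95% to 91.2%: odds-ratio test 5%; risk-difference test 25% to 38%.

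For comparison, a case without a ceiling: chronic lung disease 70% to 65% (odds ratio 0.80), others 57% to 39% (odds ratio 0.48), prevalence 20% to 40%. Power in the predicted direction is 18% to 25% on the odds-ratio scale and 23% to 31% on the risk-difference scale. Here the two scales agree in direction and are similarly weak.

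**The case against.** There is a good case for the plan as written. An interaction term in the trial's own logistic model is a valid and conventional test, consistent with the primary effect measure. SAP 4.4 does not say that its hypotheses are absolute. Protocol 10.1.1 sets the absolute difference for the overall sample size, not for subgroups. Where the protocol does quantify an effect within a subgroup (10.1.2, virus detected), it uses a relative risk and tests it with a logistic interaction. The cautious-prescribing argument can also mean that clinicians disregard the result in chronic lung disease, which would move that odds ratio towards 1, and footnote b would then point the right way. Finally, Table 2 prints percentages by arm in every subgroup, so a reader could see a fall from 90% to 83% beside one from 60% to 45%.

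Most of this stands. It shows that the test is not wrong and that the problem depends on the rates. It does not remove the gap: a directional hypothesis with no named scale cannot be judged unambiguously, and the printed percentages give neither an adjusted risk difference nor an interval for the contrast. A relative-risk reading does not close the gap either. At 90% to 83.1% the risk ratio is 0.92, against 0.75 for 60% to 45%, so it also shows a smaller effect in chronic lung disease while the odds ratios are equal.

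A reader might infer something stronger: that if the SAP's hypothesis is true, the planned test has almost no chance of showing it. The documents do not support that. It requires near-universal control prescribing in chronic lung disease, and the SAP speaks only of a tendency and gives no rate. Protocol 10.1.1 expects patients to be selected for clinician uncertainty. Examples in which the odds-ratio test finds nothing are ones where the odds ratios were set equal or nearly so, so low power there follows from the choice of rates.

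**Conclusion.** The point holds as a minor one. SAP 4.4 leaves open the scale of its directional hypotheses, and the single planned contrast is on a scale other than that of the trial's minimum important difference. If control prescribing in chronic lung disease is about 85% or more and is much higher than elsewhere, an odds ratio equal to the design effect means 9.4 points or fewer, not 15, and a smaller absolute fall can even show a stronger odds ratio. At 70% to 75% the discrepancy is only 1.0 to 2.1 points and can be ignored. Which case applies cannot be settled from the documents.

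The argument is explicit only for chronic lung disease. A reader might extend it to age and to patient–clinician disagreement, but SAP 4.4 does not rest those hypotheses on higher control prescribing, and nothing here quantifies them. The primary analysis and the sample size are unaffected. Power for a subgroup contrast is low on either scale, so the gain is in estimation and interpretation, not in detection.

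**What to change.** Keep the odds ratios and footnote b. In SAP 4.4 and Table 2, add for each subgroup the adjusted risk difference with its 95% confidence interval. For each pair of subgroups, add the difference between the two risk differences with its 95% confidence interval. Both come from marginal standardisation of the same logistic model with its interaction term.

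Add one sentence to SAP 4.4 saying that the subgroup hypotheses will be interpreted from the estimates on both scales, and not from the odds-ratio interaction p-value alone. Making the absolute scale the sole basis for judgement, or adding further interaction p-values as decisive tests, would be a trade-off and is not needed.

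The cost is a change of SAP wording and one post-estimation step per subgroup analysis, with no new data and no change to the sample size. The downside is a longer table with two scales to explain, and wide intervals on both.
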